### Analysis strategies

The main analysis will assess the effect of the interventions on the primary and secondary outcomes. Primary analysis of the outcome(s) will follow the intention to treat principle (i.e. the participants will remain in the group they were randomised to and not analysed according to the interventions actually received), and will account for clustering and stratification.

For the primary outcome (proportion of children dying before the age of 5 years), the relative risk with a 95% confidence interval will be reported, taking appropriate account of clustering. A generalised linear model (with adjustment for stratification factors) using robust standard error estimates will be used to carry out this analysis.

For secondary binary outcomes, including morbidity, maternal mortality and morbidity, institutional deliveries, home birthing practices, relative risks will be estimated in an analogous fashion. For continuous outcomes t-tests with robust SEs will be carried out. ANCOVA (with robust standard errors) will be used where baseline adjustment is required. Bootstrapping will be used for non-normal outcomes and Cox models for survival analysis. A full analysis plan will be given in the operations manual.

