## Background

### Research justification and relevant literature

Guinea-Bissau is a small country in West Africa with a population of 1.7 million. The country is very poor with GDP per capita at $352 per person. The WHO and UNICEF report that under-five child mortality is 203 per 1000 in 2004, ranking the 10^th ^highest amongst 192 countries [1].

A prospective survey conducted during 2003–2005 estimated that under-five child mortality is 308 per 1000 in rural regions of Guinea-Bissau, with neonatal mortality of approximately 70 per 1000 [Rodriguez, A., Tome, C: Seguimento e avaliacao de indicadores do plano nacional de desenvolvimento sanitario e do projecto multisectorial de luta contra sida. Bandim Health Project, 2006]. Our baseline survey in the region where this study is to be implemented found an under-five child mortality rate of 154 per 1000 as reported by women aged 12 to 49 for their 2002 to 2007 pregnancy history. While both estimates suggest very high child mortality, the difference in these estimates may reflect methodologies (prospective versus retrospective monitoring of births and deaths) and differing regional coverage. There is very little information on the causes of child deaths. The Bellagio Child Survival Study Group concluded that neonatal deaths in low income countries were mostly due to sepsis acquired around and soon after birth, birth asphyxiation, and congenital abnormalities. They estimated that diarrhoea, pneumonia and malaria cause more than three quarters of child deaths after the neonatal period [2]. The Joint United Nations Programme on HIV/AIDS estimates a relatively low 1.8% HIV prevalence in Guinea-Bissau in 2007 compared to other Sub-Saharan African countries where the overall prevalence estimate is around 6% [3].

The high child mortality in rural Guinea-Bissau is likely to be due to multiple factors. Although most of the diseases that cause child deaths are probably preventable, low income and logistics have limited the quality and availability of public healthcare. Even if clinical services were improved, poor health knowledge and education and limited number of trained health personnel, probably contribute to poor treatment seeking practices and preventable child deaths. Poor roads and remoteness also make it difficult for guardians to seek care for their children.

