### Randomisation

Clusters will be stratified according to major ethnic categories (Balanta, non-Balanta and mixed ethnicity) and to distance from a regional health centre or hospital (within walking distance or not). All 146 clusters will be randomly allocated, within these six strata, to either the intervention or control group.

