### Methods of enumerating and interviewing women during baseline survey

Six mobile survey teams were trained to enumerate women in the mapped eligible dwellings in each cluster during the baseline survey. They recorded all eligible women living in these dwellings, and recorded their full birth history and child survival records. In the case of women who are normally resident in the tabanca but not present at the time of the baseline survey, the survey team recorded their name and house location but did not list their children nor record their birth history.

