### Data collection and surveillance

#### Initial baseline survey

The initial baseline survey will be conducted before randomisation. The information from this survey will be used to define clusters and generate lists of eligible women and children. The survey will record birth and child survival histories for each eligible woman.

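### The primary model omits each cluster's pre-trial child mortality, which was recorded before randomisation: avoidable loss of precision, not an error

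*Protocol article*

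**What the plan says.** The protocol article names the primary model and its covariates under Analysis strategies: "A generalised linear model (with adjustment for stratification factors) using robust standard error estimates will be used to carry out this analysis". No other covariate is mentioned.

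Under Randomisation, three ethnic categories are crossed with two distance categories: "All 146 clusters will be randomly allocated, within these six strata, to either the intervention or control group". Mortality is not a stratification factor.

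The timing of the baseline survey is clear: "The initial baseline survey will be conducted before randomisation". On its content: "The survey will record birth and child survival histories for each eligible woman". The section on enumerating and interviewing women confirms that the teams "recorded their full birth history and child survival records". A pooled result is already reported in the Background: an "under-five child mortality rate of 154 per 1000 as reported by women aged 12 to 49 for their 2002 to 2007 pregnancy history".

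Baseline adjustment appears once, straight after the t-tests for continuous outcomes: "ANCOVA (with robust standard errors) will be used where baseline adjustment is required". The section ends: "A full analysis plan will be given in the operations manual".

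**The concern.** Past child mortality in the same villages is a natural predictor of child mortality there during the trial. It was measured before allocation, for every cluster, and allocation cannot have affected it. In a cluster trial the precision of the treatment effect depends heavily on how much true risk varies between clusters, and a cluster-level baseline of the outcome can explain part of exactly that component. Ethnicity and distance capture only what those two factors predict.

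At stake is the width of the confidence interval for the relative risk, and power if the true effect is smaller than planned. The sample size section itself allows for dilution through migration. A covariate added once outcomes are known would depart from the published primary model and invite dispute, so the choice should be fixed in advance.

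**Working it through.** **Inputs from the protocol (Sample size calculation; Table 1 for the arms).** 12 live births per cluster per year; 48 children at randomisation plus 30 births = 78 per cluster, or 70.2 after 10% loss; ICC 0.02, with 0.00644 cited from a neonatal mortality trial with larger clusters; control risk 9%, reduced by 30% to 6.3%; two-sided 5%; 73 clusters per arm.

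**Assumptions not in the documents.** About 60 baseline births per cluster (12 × 5 years, 2002 to 2007), the same ICC in both periods, and a correlation *c* between a cluster's true risks in the two periods, varied from 0.3 to 1.0.

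**The plan's own figure.** For 9% v 6.3% at 80% power, 1,521 children per arm are needed before clustering. The design effect is 1 + 69.2 × 0.02 = 2.384. Clusters per arm: 1,521 × 2.384 / 70.2 = 51.7, so 52, or 104 in total. The stated 130 is not reproduced; other standard variants give 94 to 122. The difference is conservative and does not affect this point.

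**Step 1: between-cluster share of the variance of a cluster's mortality.** m × ICC / (1 + (m − 1) × ICC) = 70.2 × 0.02 / 2.384 = 0.589. At ICC 0.00644: 0.452 / 1.446 = 0.313.

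**Step 2: reliability of the baseline cluster rate.** 60 × 0.02 / (1 + 59 × 0.02) = 1.20 / 2.18 = 0.550. At 154 per 1000, 60 births mean about 9 deaths per cluster, so the covariate is noisy.

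**Step 3: variance explained.** r² = c² × 0.589 × 0.550 = 0.324 c². The residual variance is multiplied by 1 − r².

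**Step 4: power with 146 clusters.** Effective children per arm: 73 × 70.2 / 2.384 = 2,150. SE of the risk difference: √[(0.09 × 0.91 + 0.063 × 0.937) / 2,150] = 0.0081. Then 0.027 / 0.0081 − 1.96 = 1.37, which gives 91.5%. With adjustment the SE is multiplied by √(1 − r²). The last two columns repeat this for smaller true reductions.

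| c | r² | SE ratio | Equivalent clusters, 146/(1 − r²) | Power, 30% reduction | 25% | 20% |
|---|---|---|---|---|---|---|
| no covariate | 0 | 1 | 146 | 91.5% | 78% | 58% |
| 0.3 | 0.029 | 0.985 | 150 | 92.2% | 79% | 59% |
| 0.5 | 0.081 | 0.959 | 159 | 93.5% | 82% | 62% |
| 0.8 | 0.207 | 0.890 | 184 | 96.3% | 87% | 68% |
| 1.0 (upper bound) | 0.324 | 0.822 | 216 | 98.2% | 92% | 75% |

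**Checks.**
- A beta-binomial cluster simulation (1,500 replicates per scenario) gave SE ratios of 0.99, 0.96, 0.89 and 0.84, close to the formula and slightly less favourable at c = 1.0.
- With 40 baseline births instead of 60, the variance falls by 2.4%, 6.6%, 16.9% and 26.5%.
- At ICC 0.00644 the SE falls by only 0.4% to 4.5%, and power is already about 99%.
- At an assumed ICC of 0.03, power is 83.5% without the covariate and 84.9%, 87.5%, 93.4% and 97.6% with it.

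**The case against.** The strongest reply is that nothing here is wrong. A generalised linear model adjusted for the strata, with robust standard errors, is valid and matches the randomisation. The article does not say that the strata are the only covariates allowed, and it defers a full plan to the operations manual. The first part stands in full. The second stands in part: the operations manual could hold this covariate. But the article does state the primary model with its adjustment set, and the suggestion improves that stated choice.

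A reader might infer that baseline adjustment is ruled out for the primary outcome because it is mentioned only beside continuous outcomes. The sentence does not say so; ANCOVA is simply the continuous-outcome method.

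A reader might also infer that the trial is short of power without the covariate. On the stated inputs it is not: 91.5% with 146 clusters. A shortfall needs other inputs, such as a control risk well below 9%, a higher ICC or a smaller effect.

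Nor do the documents support calling the trial dominated by between-cluster variance. The share is 59% at ICC 0.02, an estimate borrowed from another country, and 31% at 0.00644, although the protocol expects the ICC here to be the higher of the two.

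The objection that the gain is uncertain also stands. The correlation is unknown. The histories are retrospective, they are missing for women absent at the survey, many children born in 2002 to 2007 had not reached five by then, and the strata may already take part of the gain.

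Finally, chance imbalance in baseline mortality is already reflected in the confidence interval. It is not a separate flaw to be added to the precision argument.

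**Conclusion.** The point holds as a missed efficiency option, not as an error. A cluster-level baseline of the primary outcome exists from before randomisation, and the stated primary model does not use it. On the protocol's inputs, with 60 baseline births per cluster assumed, the variance reduction runs from about 3% (c = 0.3) to 32% (c = 1.0, an upper bound). Power rises from 91.5% to between about 92% and 98%. All of these are upper-side figures, for the reasons conceded above. The gain is small if the ICC is near 0.00644. It matters more if the effect is diluted: at a 25% reduction, power moves from 78% to 82% or 87% for c of 0.5 or 0.8.

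It is tempting to ask for the child's age at entry as well, since age predicts death. I do not include it. A category for children born during follow-up is defined after randomisation for many of them (30 of the 78 expected per cluster are births in the trial period), and the package includes antenatal and delivery care that could affect live births. No gain from that covariate has been shown.

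**What to change.** Pre-specify, in the primary model and beside the strata, one cluster-level covariate: the log of a shrunken estimate of baseline under-five mortality from the pre-randomisation birth histories, with cluster-robust standard errors. Shrinkage is needed because each cluster contributes only about 9 baseline deaths. State the estimator in advance, including how children who had not reached five at the survey are handled. Keep the strata-only model as a sensitivity analysis.

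The cost is a sentence in the analysis section, a little more analysis work and one extra cluster-level parameter, which 146 clusters carry easily. No new data are needed. If the correlation turns out low, almost nothing is lost.

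### The method named for continuous outcomes, a t-test with robust standard errors, has no term for the six randomisation strata when read literally, so its standard errors may be too large

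*Protocol article*

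**What the plan says.** All references are to the protocol article.

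- **Randomisation.** Clusters are stratified by three ethnic categories and by whether a health centre or hospital is within walking distance: "All 146 clusters will be randomly allocated, within these six strata, to either the intervention or control group".
- **Analysis strategies, scope.** "The main analysis will assess the effect of the interventions on the primary and secondary outcomes". The next sentence begins "Primary analysis of the outcome(s) will follow the intention to treat principle" and ends "and will account for clustering and stratification".
- **Analysis strategies, primary outcome.** "A generalised linear model (with adjustment for stratification factors) using robust standard error estimates will be used to carry out this analysis".
- **Analysis strategies, secondary binary outcomes.** "relative risks will be estimated in an analogous fashion", which carries the strata adjustment over from the primary outcome.
- **Analysis strategies, continuous outcomes.** "For continuous outcomes t-tests with robust SEs will be carried out". ANCOVA with robust standard errors is added for cases that need baseline adjustment. Bootstrapping is assigned to non-normal outcomes and Cox models to survival analysis.
- **Analysis strategies, closing sentence.** The full analysis plan is left to the operations manual, which is not shown.

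**The concern.** The section makes a two-part commitment, to clustering and to stratification, and then names a method for each type of outcome. For binary outcomes the named method meets both parts. For continuous outcomes the robust standard error can meet the clustering part, but nothing in the sentence meets the stratification part. A t-test as ordinarily understood compares two arms and has no other term. The one covariate-adjusted method offered for these outcomes is tied to baseline values. An analyst who follows the sentence to the letter would drop the strata for this one class of outcome.

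Stratified randomisation balances the arms on the strata, so differences between strata largely cancel out of the arm comparison. If the analysis leaves the strata out, that variation stays in the residual and enters the standard error. The interval is then wider than the design warrants, and the test rejects less often than its nominal 5%. Ethnic category and distance to care were chosen as stratifiers, so some relation to outcomes is plausible, but the document gives no figure for it.

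**Working it through.** **Plan's own figure.** There is none to reproduce. The protocol gives no standard deviation, intraclass correlation, respondent number or variance share for any continuous outcome.

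**Inputs.**
- From the protocol: 146 clusters, six strata, two-sided 5% level, and an intraclass correlation of 0.02 (given for child death; used here as the lower end).
- Assumed: intraclass correlation ρ up to 0.05; respondents per cluster m from 7 to 50; share R² of between-cluster variance explained by the strata from 10% to 30%.
- The lower end of m comes from the Sample size calculation section. It expects 48 + 30 = 78 children per cluster and 9% deaths in control clusters, so 78 × 0.09 ≈ 7 deaths per control cluster. That is the relevant number for age at child death.

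**Formulas.**
1. Share of the variance of a cluster mean that lies between clusters: s = ρm / (1 + (m − 1)ρ).
2. True variance of the arm difference relative to what the unstratified analysis reports: v = 1 − R²s.
3. Ratio of reported to needed interval width: w = 1/√v.
4. True type I error: 2 × P(Z > 1.96w).

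**Central case (ρ = 0.05, m = 50, R² = 0.20).** s = 2.5/3.45 = 0.72; v = 1 − 0.20 × 0.72 = 0.855; w = 1.08; true error = 2 × P(Z > 2.12) = 3.4%.

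**Range.**

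| ρ | m | R² | s | v | Interval wider by | True type I error |
|---|---|---|---|---|---|---|
| 0.02 | 7 | 0.10 | 0.125 | 0.988 | 0.6% | 4.9% |
| 0.02 | 20 | 0.10 | 0.290 | 0.971 | 1.5% | 4.7% |
| 0.05 | 7 | 0.20 | 0.269 | 0.946 | 2.8% | 4.4% |
| 0.05 | 50 | 0.20 | 0.725 | 0.855 | 8% | 3.4% |
| 0.05 | 50 | 0.30 | 0.725 | 0.783 | 13% | 2.7% |
| any | any | 0 | – | 1 | 0% | 5.0% |

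**Check by simulation.** 146 clusters of 70 in six near-equal strata were randomised 1:1 within strata, with 3000 runs per setting and ρ from 0.02 to 0.10. A comparison on arm alone with cluster-robust standard errors was set against the same model plus stratum terms.
- *Strata explain 0%:* no difference.
- *Strata explain 20%:* without the strata, the reported standard error was 7% to 10% larger and type I error was 3.4% to 3.9%, against about 5% with them. Power was 73% to 78%, against 80% to 82%.
- *In every setting:* the actual spread of the estimates was the same with and without the strata. Only the reported standard error differed.

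**The case against.** The strongest reply is that a t-test with robust standard errors is, in practice, a regression on arm with a cluster-robust standard error, to which stratum terms can be added. The general sentence on clustering and stratification can be read as governing the short list of methods, since the bootstrap and Cox clauses do not mention strata either. The full analysis plan is in a manual that is not shown, and a condensed article may leave model terms to it.

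Much of this stands. A reader might infer that the named method cannot use the strata, that the section contradicts itself, or that precision is thrown away. The document supports none of the three. Strata terms can be added. Nothing in the section rules them out. The estimate itself is no less precise without them; only its reported standard error is inflated.

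It is also fair that few outcomes are touched. In Outcomes of the study, the primary outcome is binary and almost all secondary outcomes are proportions, prevalences or rates. Age at death and costs are the evident continuous ones. Both may be skewed, so they may go to the bootstrap or, for age at death, to a Cox model.

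The reply does not remove the point. The section is not merely silent: it names a specific method for this class of outcome. It spells out strata adjustment for the primary outcome, carries it to the binary secondary outcomes, and does not carry it to the continuous ones. Once stratum terms are added, the procedure is a stratified regression, and the text should say so.

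**Conclusion.** The point holds as a minor one. Followed literally, the sentence on continuous outcomes leaves out the six randomisation strata, although the same section undertakes to account for them. The estimate is essentially unchanged. If ethnic category or distance predicts the outcome, the standard error is overstated, by roughly 1% to 13% over the assumed range, with a true type I error of about 4.9% down to 2.7%. These sizes rest wholly on the assumed intraclass correlations, respondent numbers and variance shares; with no prognostic strata the effect is nil. The error is conservative and creates no false positives. The primary outcome and the secondary binary outcomes are not affected.

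**What to change.** Replace the t-test sentence with a statement that continuous outcomes will be compared by linear regression on arm and the stratification factors (ethnic category and walking distance), with cluster-robust standard errors, reporting the adjusted mean difference and its 95% confidence interval. State that the ANCOVA includes the same strata terms.

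The cost is one or two sentences in Analysis strategies, matched in the operations manual. No extra data are needed, because the strata are known for every cluster at randomisation. With 146 clusters, the few added terms have no material cost: in the simulated settings where the strata explained nothing, the standard errors with and without them were the same.

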### Ethical approval

The trial protocol has received ethical approval from the Ministry of Health, Department of Hygiene and Epidemiology Centre for Coordination of the Research in Guinea-Bissau (reference number: 021/2007) as well as from the ethics committee of the London School of Hygiene and Tropical Medicine (reference number: 5173).

## Discussion

### Administrative Structure – The implementation teams

Independent service delivery and research teams will be responsible for the implementation of interventions and for the data collection needed to analyse the trial outcome.

### The service delivery team

The service delivery team will be responsible for implementing the key components of the project, but they will have no responsibility for data gathering or processing used to analyse outcomes. The team will have the following members:

#### Health club supervisor and trainers (3 + 22)

Three health club supervisors will monitor the trainers. There will be 22 trainers during the first year managing an average of six health clubs each. The trainers will be given a 6 week training course ahead of their first health clubs.

#### Nurse-Trainers (9)

Health professionals will be hired to train village health workers, and act as mentors and support for those people, during the first year of the intervention. The mentors will organize regular individual and group meetings with village health workers to discuss problems, and also visit village health workers in their community and operate mobile clinics. They will also coordinate training for village health workers.

#### Village health workers (250–300)

One to four village health workers who are resident in the cluster and chosen by health clubs will be trained in maternal and child health. The numbers chosen will depend on the size of the cluster and the distance needed to travel to households within the cluster. Generally at least one person will be trained in child health, and at least one person will be trained in safe pregnancy, safe delivery and care of the newborn.

#### Tie-ups with local clinics and hospitals

One or more reference centres will be chosen to manage various services that may be required by children and pregnant mothers. These services include:

• Services for normal and caesarean deliveries at hospitals that serve the trial communities

• A hostel for high risk women, so that they can travel ahead of delivery, near the hospital

• Primary and secondary pre and post-natal clinical and hospital care that may be needed for pregnant women and neonates

• Emergency services for children

